## Abstract

**Background:**

Non-steroidal anti-inflammatory drugs (NSAIDs) are a common cause of renal damage, especially when taken together with angiotensin-converting enzyme inhibitors (ACE-i) or angiotensin II receptor blockers (ARBs) plus a diuretic — a combination known as the “triple whammy.” New Zealand patients are at high risk of the “triple whammy” because they can easily purchase NSAIDs without a prescription and in nonpharmacy retail settings (eg, the supermarket), there is no legal requirement to include patient information sheets with medication, and direct-to-consumer drug advertising is permitted. A patient information package has been developed for those at greatest risk of the “triple whammy,” consisting of a printable PDF and an interactive online learning activity. This information package aims to inform patients about their elevated risk of harm from NSAIDS and discourage use of NSAIDs. A randomized control trial was planned to assess the effect of the information package.

**Objective:**

This study aims to pilot the trial procedures for recruiting patients and providing patient information online and to assess the acceptability of the patient information package.

**Methods:**

A two-armed randomized feasibility trial will be undertaken in Northland, New Zealand. We will recruit 50 patients who are at least 18 years old from those who have signed up to receive email alerts through their general practice. Patients eligible for this study have been prescribed an ACE-i or ARB plus a diuretic in the past 3 months. They will be randomly allocated to 2 study arms. The intervention arm will receive access to an information package plus usual care; the control arm will receive usual care alone. Online surveys will be used to assess NSAID knowledge and NSAID use at baseline and after 2 weeks for both arms. The intervention arm will also evaluate the information package in an additional survey based on Normalization Process Theory (NPT) concepts. We will report the number and proportion of participants who are eligible and consent to participate in the trial. Response and drop-out rates will be reported for each trial arm. The numbers of patients who interact with the education package will be reported together with the patient evaluation of it.

**Results:**

Funding has been obtained from the Health Research Council of New Zealand (HRC 18-031). The University of Otago Human Research Ethics Committee (H21/016) has approved this trial. Consultation has been undertaken with The Ngai Tahu research consultation committee. The trial commenced on April 12, 2021.

**Conclusions:**

This feasibility trial will test the study processes prior to commencing a randomized controlled trial and will determine the acceptability of the patient information package. We anticipate this work will provide useful information for other researchers attempting similar work.

**International Registered Report Identifier (IRRID):**

PRR1-10.2196/29161

## Introduction

Non-steroidal anti-inflammatory drugs (NSAIDs) are a common cause of renal damage [1]. The risk of renal injury dramatically increases when NSAIDs are taken together with angiotensin-converting enzyme inhibitors (ACE-i) or angiotensin II receptor blockers (ARBs) plus a diuretic [2] — this is known as the “triple whammy” combination. Despite this issue being well known and publicized heavily to prescribers in recent years, coprescribing of these medications is still common in New Zealand; 2017 data suggest more than 26,500 patients were prescribed these medications concurrently, with the majority of these patients aged over 65 years [3,4].

While prescribers should be well aware of the dangers of combining NSAIDs with other medications that alter renal perfusion, patients may not be [5-7]. The true extent of simultaneous use of these medications is unknown. Nonprescription use of NSAIDs may be high in New Zealand. This is due to the easy availability of NSAIDs for patients to purchase without a prescription and in nonpharmacy retail settings (eg, the supermarket), no legal requirement to include patient information sheets with medication, and direct-to-consumer drug advertising [8]. Given these issues, it is important to maximize the opportunities to advise patients about the potential risks of taking anti-inflammatories as part of the “triple whammy.”

Existing information for patients is generic and not generally considered fit-for-purpose [8]. Tailoring medication information for patients may improve the quality and usefulness of information, as well as improve patient knowledge [9,10]. However, examples of personalized medication information are rare [11]. Most patients consider doctors to be their main source of health information. Patients want to be able to share that information with their whanau (family) as well as health professionals [12,13], but doctors do not always provide patients with that information [14,15]. Doctors find communicating risk information difficult [16,17], and communicating potential risks of NSAIDs may be incomplete [18]. Time, low health literacy levels, and lack of patient interest have been suggested as additional barriers to communication [13].

Providing information directly to patients may help address some of those issues; however, information must be provided at an appropriate health literacy level. New Zealanders typically have low levels of health literacy — over half of all adults surveyed had skills “insufficient to cope with the health literacy demands they typically face” [19]. When the health literacy study results were broken down by ethnicity, 75%-80% of Maori (the indigenous people of Aotearoa, New Zealand) and 90% of Pasifika (people living in New Zealand who migrated from or have ancestry in the Pacific Islands) had low health literacy levels [19]. Health literacy has been identified as a cause of health disparities [20], and decision support tools can help address deficits in health literacy [21,22]. Self-efficacy, a patient’s belief in their ability to undertake and successfully complete a task, is another factor highly associated with optimal medication use [23,24].

Most medication information for patients is in leaflet form, with patient information resources becoming increasingly available online. Patients search for high-quality, reputable information, but find it hard to judge the quality of the information they find online [13]. A few studies have examined novel modalities of delivering health information to patients, but there is room for further research to evaluate the efficacy of alternative media modalities [25,26].

Conporto Health Event Detection & Mitigation (Conporto) is a software package that detects whether general practice patients are at risk of harm from their prescribed medications [27]. The current system operates in real time to detect if there is a risk of harm from prespecified conditions, for example, if methotrexate is prescribed without a coprescription for folic acid or if allopurinol is prescribed at a dose of >200 mg/day to a patient with chronic renal insufficiency. Clinicians are informed of each alert and then decide whether to take action or inform patients. Conporto has developed the capacity to contact patients directly via text and email, with patient consent. This patient contact is triggered when a patient requests a prescription from their general practice and is currently used to inform patients that their prescription is ready for collection. This function could also be used to provide patients with more information about their medications.

We have developed a printable information sheet and an online learning activity for patients. Patients, general practitioners, pharmacists, and a patient education provider have contributed to the development of these resources, which aim to inform patients about their elevated risk of harm from NSAIDs and discourage them from using over-the-counter NSAIDs. A randomized controlled trial (RCT) was proposed to examine the effect of giving at-risk patients this information directly, without needing their health care practitioners to provide it. This trial aims to assess the impact of providing an information package about avoiding anti-inflammatory medicines to patients at risk of renal damage from the “triple whammy,” in particular, the impact on anti-inflammatory knowledge and self-reported behavior. However, we have a number of concerns that we need to address before carrying out the full RCT.

First, it is unknown if our recruitment methods will be successful in enrolling a representative sample of the target population. Second, a low response rate of online surveys is a common concern. Having a better understanding of the survey response rate will help us determine the number of participants needed for the full trial. Third, while we have developed the information package with some patient input, it has not been formally evaluated by patients. Fourth, we do not know whether the survey questions are appropriate to assess the impact of the intervention. Therefore, we plan to conduct this randomized feasibility trial to assess the feasibility of the intervention and pilot the recruitment methods and the use of surveys for assessing the impact of the intervention. The results of this feasibility trial will help refine our methods prior to commencing a definitive RCT.

The primary aim of this study is to assess the feasibility of conducting an RCT. The RCT will investigate the effect of providing a patient information package about NSAIDs to patients at increased risk of renal damage because of their medications. The feasibility trial will elucidate any issues that could impair our capacity to answer the aims of the full trial.

The feasibility trial aims to (1) pilot the procedures for recruiting patients and providing patient information online to assess the number of eligible participants and the recruitment rate, assess the characteristics of participants who are enrolling in the trial, identify any technical challenges for patients assessing information online, and assess the drop-out rate in each group; (2) assess the acceptability of the patient information package to assess if patients trust and understand the information provided and think it is relevant to them; and (3) pilot the use of the survey for assessing the effects of providing patients information about the risk of NSAIDS to obtain preliminary data of the survey responses to help with sample size calculation in the full trial, assess the response rates of the surveys, and assess the suitability of survey questions to measure the impact of the intervention.

## Methods

This will be a two-armed randomized feasibility trial. The trial will be conducted according to the steps outlined in Figure 1.

**Figure 1 figure1:**
[figure not shown]
Flow chart of study protocol.

### Recruitment

Conporto is used by general practices across New Zealand. Patients attending general practices using Conporto in the Northland region will be eligible to participate in the randomized feasibility trial. Northland was chosen as Conporto is used widely in the region. Northland is a subtropical region in New Zealand, with a population of 179,000. Compared to the rest of New Zealand, Northland is more rural, is poorer, and has a higher proportion of people of Maori ethnicity [28]. Recruitment will be undertaken at the individual level. We aim to recruit 50 patients (25 patients in each trial arm) to pilot the use of the surveys. Participants will be allocated a unique study identification number to preserve anonymity.

Patients will be identified as having increased risk of harm from NSAIDs from their current prescriptions. Patients prescribed at least 2 of the 3 “triple whammy” medications (ie, an ACE-i or ARB plus a diuretic) will be identified by Conporto. Patients will be eligible to participate in this study if they were prescribed these medications concurrently in the past 3 months, are over 18 years old, and if they have signed up to receive Conporto’s email messages. Textbox 1 describes participant inclusion and exclusion criteria. All eligible patients will be invited to participate in the study via email from Conporto.

Participant eligibility criteria.
**Inclusion criteria**
Age 18 years or olderAngiotensin-converting enzyme inhibitor (ACE-i) or angiotensin II receptor blockers (ARB) + diuretic in the past 3 monthsSigned up to receive Conporto alerts
**Exclusion criteria**
Fails to complete enrollment

### Randomization and Blinding

Following recruitment to the study, patients will be automatically randomized 1:1 to either the control or intervention group within each practice. Patients will not be advised to which group they are allocated. Stata software will be used to generate the randomization sequence, which will be allocated using REDCap (Research Electronic Data Capture) software. REDCap software will also be used to administer all the surveys. REDCap is a secure, web-based survey tool suitable for data requiring high-security storage (ie, patient data). Nonrespondents at each stage will be emailed 2 further invitations to participate, at 1-day intervals.

### Baseline Assessment

The study invitation email will contain a link to the baseline assessment (Multimedia Appendix 1). The first page of the assessment contains a consent form approved by the University of Otago Human Ethics Committee. Once the consent form is completed, the rest of the form opens automatically to request demographic information, information about current medications and NSAID use, a validated single-item health literacy assessment [29], a validated 4-item medicine use and self-efficacy questionnaire [23], a validated NSAID knowledge assessment [30], and a self-report of NSAID use in the preceding fortnight.

### Study Intervention

Within 24 hours of completing the baseline assessment, intervention group patients will be emailed a link to a webpage containing a fully accessible, online, interactive learning activity and a downloadable PDF [31]. Patient information about avoiding anti-inflammatories and an online, interactive learning activity have been developed by SL in conjunction with the Health Navigator editorial board, their pharmacist, and the Health Navigator patient panel in an iterative process. The webpage is hosted by Health Navigator New Zealand, a nonprofit initiative that provides curated health information overseen by the Health Navigator Charitable Trust. Both the control and intervention groups will receive usual general practice care from their own primary care team during the trial. After the trial is completed, control group patients will also be sent an email with a link to the information package, so all patients in the study eventually have access to that resource.

### Follow-Up Assessment

All patients will be sent a follow-up survey after 2 weeks that repeats 2 survey items from the baseline assessment: the validated NSAID knowledge assessment [30] and the self-report of NSAID use in the preceding fortnight

Patients in the intervention arm will also complete an additional survey to evaluate the information package. This evaluation survey is based on Normalization Process Theory (NPT) concepts (Multimedia Appendix 1) [32]. NPT has been successfully used in the assessment and implementation of multiple patient-facing complex health interventions [33-35] and to evaluate other primary care initiatives aiming to reduce kidney injury [36,37].

### Measures

We will report the number and percentage of patients who are eligible to participate in the trial and those who consent to participate. For participants in each of the study arms, we will report the response and drop-out rates for each of the surveys. The number of patients who open the information package will also be recorded via the website analytic data from the Health Navigator website [38]. The numbers of patients who interact with the education package will be reported, together with the patient evaluation of it. NSAID knowledge scores and self-reports of NSAID use will be measured at baseline and 2-week follow-up.

### Statistical Analysis

Descriptive analyses will be carried out to summarize the characteristics of the participants in each study arm. Preliminary data will be obtained for the NSAID knowledge scores and self-reported NSAID use at baseline and follow-up to guide sample size calculation for the full trial. If numbers allow, linear mixed models will be used to compare the changes in the mean score on the NSAID knowledge questionnaire and self-reported NSAID use between the 2 arms.

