### Strengths and Limitations

This trial will evaluate the entire implementation process, testing trial processes and the acceptability of the intervention. The results of this feasibility trial will ensure best use of limited health research funding for any future similar studies. Publication of this work will help other researchers considering conducting similar patient-focused research.

Language, education, and technology can be barriers to health literacy [39]. The main limitation of this research is that patients with the greatest barriers to health literacy are likely to experience those same barriers in accessing the proposed intervention and participating in this research project. The research project and proposed intervention were developed only in English due to financial constraints. If this intervention is successful in English on full testing, it is hoped funding will be made available to translate the intervention into different languages (eg, Maori, Samoan, and Tongan in the first instance).

A potential risk of this work is that patients experience anxiety or distress when they realize they are at increased risk of harm from medication. This risk is mitigated by the ubiquitous nature of health information readily available to patients and the repeated encouragement for participants to discuss their concerns with their health care providers.

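### The plan can report uptake, but as written it cannot show whether enrolled patients represent the target population, which is its first stated concern

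*Protocol article*

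**What the plan says.** All of the following is in the protocol article.

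- **Introduction, reasons for the trial.** Four concerns are to be addressed before the full RCT. The one listed first is: "First, it is unknown if our recruitment methods will be successful in enrolling a representative sample of the target population".
- **Introduction, feasibility aims.** The matching aim is to "assess the characteristics of participants who are enrolling in the trial". No comparison group is named.
- **Recruitment and Textbox 1.** Conporto identifies patients on the drug combination from their prescriptions. They are eligible only "if they have signed up to receive Conporto’s email messages".
- **Baseline Assessment.** "Once the consent form is completed, the rest of the form opens automatically to request demographic information".
- **Measures.** "We will report the number and percentage of patients who are eligible to participate in the trial and those who consent to participate".
- **Statistical Analysis.** "Descriptive analyses will be carried out to summarize the characteristics of the participants in each study arm".
- **Strengths and Limitations.** The article expects that "patients with the greatest barriers to health literacy are likely to experience those same barriers in accessing the proposed intervention", and it expects the same barriers to affect taking part in the study.

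**The concern.** Representativeness is a relation between the enrolled group and a population. A table of characteristics by randomised arm compares two halves of the enrolled group with each other. It describes baseline balance and carries no information about who was missed.

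Two filters act before randomisation: signing up for Conporto email, and responding and consenting. For patients lost at consent, the plan yields a count. For at-risk patients who never signed up, it yields not even that, because they fall outside the eligible denominator.

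The trial is meant to inform a nationwide RCT using this recruitment route. The article reports low health literacy in 75%-80% of Maori and 90% of Pasifika, and names selective reach as its main limitation. It therefore predicts selection but plans no way to see how large it is. The team could finish knowing how many patients enrolled without knowing whether the route under-enrols the groups it is most concerned about.

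**Working it through.** The plan states no figure on this point, and the target of 50 (25 per arm) comes with no precision calculation, so there is nothing to reproduce. The check is a comparison of the text, followed by two illustrations.

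**1. What is known about each group under the plan**

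| Group | Number | Characteristics |
|---|---|---|
| At-risk patients not signed up to email | not planned | not planned |
| Eligible, not consenting | yes, by subtraction (Measures) | none; demographics follow consent (Baseline Assessment) |
| Enrolled | yes | yes, by arm (Statistical Analysis) |

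Only the last row has characteristics, so no comparison across rows is possible from the planned data.

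**2. Counts cannot stand in for characteristics**

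Assumed for illustration: 500 eligible, of whom 30% (150) belong to a subgroup of interest. The document gives only the target of 50 enrolled.

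Overall uptake = 50/500 = 10% in every row below.

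| Subgroup members among the 50 | Share of sample | Subgroup uptake | Uptake in the other 350 |
|---|---|---|---|
| 15 | 15/50 = 30% | 15/150 = 10.0% | 35/350 = 10.0% |
| 5 | 5/50 = 10% | 5/150 = 3.3% | 45/350 = 12.9% |
| 1 | 1/50 = 2% | 1/150 = 0.7% | 49/350 = 14.0% |

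The planned outputs would show the overall 10% and the share of the sample. They would not show the 30% in the pool, without which none of the three rows can be called representative or selective.

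**3. What a comparison could detect with 50 participants**

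Wilson interval: centre = (p + z²/2n)/(1 + z²/n); half-width = z√(p(1−p)/n + z²/4n²)/(1 + z²/n), with z = 1.96.

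- 10/50 (p = 0.20): centre 0.221, half-width 0.109, giving 11.2% to 33.0%.
- 15/50 (p = 0.30): 19.1% to 43.8%.
- One arm only, 8/25 (p = 0.32): 17.2% to 51.6%.

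The interval is about 25 percentage points wide for the 50 (43.8 − 19.1 = 24.7) and about 34 for one arm (51.6 − 17.2 = 34.4), so the arms should be pooled.

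Now set the sample share against a known pool share, taking assumed values of 35% and 20%:

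- 10/50 against 35%: difference 20 − 35 = −15 points, 95% CI (11.2 − 35) to (33.0 − 35) = −23.8 to −2.0.
- 11/50 (Wilson 12.8% to 35.2%) against 35%: difference −13 points, 95% CI −22.2 to +0.2.
- 10/50 against 20%: difference 0, 95% CI −8.8 to +13.0.

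The same 10 of 50 is compatible with a shortfall or with none, depending on a pool share the plan does not collect. One more patient moves the first interval across zero, so a 15-point gap is at the edge of what 50 participants can show.

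**The case against.** The strongest objection is that this is a condensed article. Its analysis section is three sentences long, and a full protocol or SAP could add a comparison table. Describing participants by arm is standard and does not exclude other tables. The stated aim is also narrower than the concern that motivates it, since it asks only for the characteristics of those enrolling, which the plan delivers. By-arm counts can be summed, and the article cites regional and prescribing data that might serve as a rough comparator.

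Part of this stands. The by-arm sentence is not wrong in itself, and an outside comparison could still be made later. What remains is that the article itself sets out the concern, the aim, the measures, the timing of data collection and the analysis, and these do not connect. The gap lies partly in data collection: no analysis document can tabulate characteristics of non-enrolled patients if none are obtained.

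Several stronger readings are tempting, and the document does not support them:

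- *The recruitment decision would rest on no evidence.* Eligibility and consent counts, response and drop-out rates are all planned, and they inform uptake. They are silent only on selectivity.
- *The article links low health literacy to older and rural patients.* Its subgroup figures cover Maori and Pasifika only. Age appears as a feature of patients co-prescribed these drugs, and rurality as a feature of Northland.
- *Conporto can supply ethnicity.* The article does not say so, and Conporto covers only the practices that use it.
- *Rates by ethnicity and age could be re-weighted to the nation.* With 50 participants this is not credible. In a subgroup of 10, follow-up of 8/10 has a Wilson 95% CI of 49% to 94%.

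**Conclusion.** The concern holds in a limited form. The article puts enrolling a representative sample at the head of the four matters it wants settled before the full RCT, yet plans characteristics only for consented participants by arm, and only numbers and percentages for the eligible and consenting. Followed as written, the trial can report uptake but cannot judge selectivity at email sign-up or at consent.

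This means unanswered by the planned data, not unanswerable, since an outside comparator could be added. The stakes are moderate. Safety and the randomised comparison are unaffected, but one of the four stated reasons for running the trial is left without a result. The conclusion rests on the text of the article; the 500, 30%, 35% and 20% used above are assumptions for illustration only. If the unseen full protocol or SAP already contains the comparison, the remaining task is to align the article's Measures and Statistical Analysis sections with it.

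**What to change.** In Measures and Statistical Analysis, add a descriptive comparison with three columns: (a) all at-risk patients whom Conporto identifies in the participating practices, where available; (b) those signed up to email and invited; (c) all enrolled participants, arms pooled. For (a) and (b), request anonymous aggregate counts by age band, sex and practice, and by ethnicity if Conporto holds it. Report (c) against (b), and (b) against (a), as differences in percentage points with 95% CIs and without hypothesis tests. If Conporto cannot supply the counts, compare (c) with published regional figures and state that these describe the general population, not the at-risk one. Keep the by-arm table for baseline description. Do not attempt re-weighting to the national population.

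The cost is one aggregate data request, possibly subject to ethics approval because it concerns people who have not consented, and one extra table. No patient contact is needed, so the request could be made although the trial has begun. State in advance that 50 participants will reveal only large departures.

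### The planned comparison of changes in knowledge score is most naturally a change-score analysis; adjusting for baseline would be more precise at almost no cost (minor)

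*Protocol article*

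**What the plan says.** The between-arm analysis of the knowledge score is one sentence in Statistical Analysis: "linear mixed models will be used to compare the changes in the mean score on the NSAID knowledge questionnaire" between the two arms. It is conditional, opening with "If numbers allow, linear mixed models will be used". The sentence does not say whether baseline enters as an outcome or as a covariate, whether the arms share a baseline mean, which random effects are used, or whether practice is in the model.

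Three other statements bear on it:

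- Measures gives exactly two time points: "NSAID knowledge scores and self-reports of NSAID use will be measured at baseline and 2-week follow-up".
- Randomization and Blinding says that "patients will be automatically randomized 1:1 to either the control or intervention group within each practice".
- Recruitment gives the size, without a power or precision basis: "We aim to recruit 50 patients (25 patients in each trial arm) to pilot the use of the surveys".

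On purpose, the Introduction states that "The primary aim of this study is to assess the feasibility of conducting an RCT". The scores themselves have a planning role: "Preliminary data will be obtained for the NSAID knowledge scores and self-reported NSAID use at baseline and follow-up to guide sample size calculation".

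**The concern.** A statistician told to compare changes between arms with a mixed model would ordinarily fit arm, time and arm-by-time, and report the interaction. With two time points and complete data, that interaction is the difference in mean change scores. The model leaves the baseline difference between arms free, although randomisation makes the true baseline means equal. Any chance imbalance at baseline is then subtracted in full, whatever the correlation between the two measurements. If that correlation is below 0.5, the result is less precise than comparing follow-up scores alone.

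At stake is the width of the interval from a trial with at most 25 per arm, and which summary figures are carried forward. A baseline-adjusted design for the full trial needs the SDs and the baseline to follow-up correlation, and the sentence does not lead the analyst to report that correlation.

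**Working it through.** **Inputs from the article.** 25 patients per arm; 1:1 allocation of individual patients; two measurements of the knowledge score. The article has no power or precision figure to reproduce.

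**Assumptions.** Equal SD at both times, set to 1, so results are in SD units; r from 0 to 0.95; two-sided 95% intervals; for the interval example, 20 completers per arm.

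**Formulas.** With n per arm, N = 2n, and SD s, the variance of the between-arm difference is:

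- follow-up only: 2s²/n
- change score: 4s²(1−r)/n
- baseline-adjusted: 2s²(1−r²)/n, times 1 + 1/(N−4) for estimating the slope in a small sample

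The large-sample ratio of adjusted to change is (1−r²)/[2(1−r)] = (1+r)/2. The change score beats follow-up alone only if 2(1−r) < 1, that is, if r > 0.5.

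**Results at n = 25** (small-sample factor 1 + 1/46 = 1.022):

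| r (assumed) | SE, change | SE, adjusted | Ratio (1+r)/2 | Ratio with small-sample factor | Ratio, 20,000 simulated trials |
|---|---|---|---|---|---|
| 0.3 | 0.335 | 0.273 | 0.65 | 0.66 | 0.67 |
| 0.5 | 0.283 | 0.248 | 0.75 | 0.77 | 0.76 |
| 0.7 | 0.219 | 0.204 | 0.85 | 0.87 | 0.87 |
| 0.9 | 0.126 | 0.125 | 0.95 | 0.97 | 0.97 |

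For comparison, follow-up alone has SE 0.283 at every r.

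**Where the gain ends.** At r = 0.95 the ratio with the small-sample factor is 0.996, 1.002 and 1.012 for 25, 20 and 15 per arm. Adjustment therefore gains at any r below about 0.95, and beyond that the loss is about 1% or less.

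**Interval width, 20 completers per arm, r = 0.5.**

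- Change: SE = √(4 × 0.5/20) = 0.316; t on 38 df is 2.024; half-width 0.64 SD.
- Adjusted: SE = √(2 × 0.75/20 × (1 + 1/36)) = 0.278; t on 37 df is 2.026; half-width 0.56 SD.

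**Model equivalence.** In one simulated data set (25 per arm, r = 0.5, true difference 0.5 SD):

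| Model | Estimate | SE |
|---|---|---|
| Mixed model, arm-by-time | 0.515 | 0.246 |
| Change-score regression | 0.515 | 0.246 |
| Mixed model, common baseline mean | 0.476 | 0.212 |
| ANCOVA on baseline | 0.473 | 0.207 |

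The first two coincide and the last two nearly coincide. Choosing a mixed model does not settle the matter; what matters is whether it constrains the baseline means.

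**The case against.** The strongest reply is that the article fixes a linear mixed model, not a change-score analysis. A mixed model with a common baseline mean also compares changes between arms, so it fits the sentence as written, and a condensed article may leave the exact form to a fuller document. This stands in part: the sentence does not exclude the better model. It does name the contrast as change, however, and its natural reading is the less precise model.

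It is also fair to say that the comparison is conditional and secondary to feasibility, and that a half-width of 0.56 rather than 0.64 SD alters no decision stated in the article. That limits the importance.

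A reader might infer three stronger things that the document does not support:

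- **That the plan leaves practice out of the analysis.** The text is silent, and a mixed model can carry a practice term. The number of practices among the 50 patients is not given, so it is unknown whether a random practice effect could be estimated.
- **That the baseline score is thrown away.** A change score does use it, with a fixed slope of 1, and is better than follow-up alone when r exceeds 0.5. The use is inefficient, not absent.
- **That the full trial will be oversized.** The article nowhere says that it will be sized on the SD of change. Scores at both times are to guide the calculation, and these yield both SDs and r whichever model is fitted to the pilot.

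**Conclusion.** The point holds as a minor one. On its natural reading, the planned comparison equals a difference in mean change scores and has 2/(1+r) times the large-sample variance of a baseline-adjusted comparison. With 25 per arm, adjustment lowers the variance by about 34%, 23% and 13% at r = 0.3, 0.5 and 0.7.

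The size depends on r, which the article does not give, and on equal SDs at the two times. The direction does not depend on knowing r unless it is about 0.95 or more. The finding concerns the knowledge score only; the same sentence also covers self-reported NSAID use, which was not examined here.

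**What to change.** Reword the sentence in Statistical Analysis along these lines:

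*If numbers allow, the knowledge score at 2 weeks will be compared between arms in a linear mixed model of the baseline and follow-up scores, with a common baseline mean for the two arms and, if the number of practices allows, a term for practice. The difference will be given with its 95% confidence interval. The SD at each time and the baseline to follow-up correlation will be reported to inform the size of the full trial.*

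The common-baseline mixed model is preferable to ANCOVA on completers. It keeps participants who answer only the baseline survey, and survey non-response is a concern that the Introduction itself raises. The two approaches are similar only without drop-out. The practice term is requested because randomisation is within practice.

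The cost is a change of wording and about one degree of freedom. No further data or software are needed.
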